### Sample size

The predicted 6-month ongoing pregnancy leading to a live birth rate for regular MOH-IUI treatment is 30% based on Dutch trials that compare MOH-IUI treatment with expectant management or IVF treatment for couples with unexplained subfertility.^20 21^ Based on the meta-analysis performed by Green *et al* and our own updated meta-analysis, the expected 6-month ongoing pregnancy leading to a live birth rate in the LPS group is approximately 39% (Green review; overall live birth rate RR (relative risk) 1.76 (95% CI 1.29 to 2.40); Casarramona updated review; cumulative live birth rate (up to six cycles) RR 1.49 (95% CI 1.17 to 1.90)).^16 17^ The a priori sample size calculation showed that 479 couples in each treatment arm would provide 80% power, with confidence level 95% to detect the predicted difference of 9% in cumulative live birth rate. To correct for potential dropout (±5%), the aim is to include a total of 1008 patients (504 patients in both groups).

### Data collection and data analysis

Data will be collected in a web-based registration system.^22^ Database cleaning will be carried out by internal consistency checks and identification of database entries outside expected ranges. All statistical analysis will be done according to the intention-to-treat principle. Primary and secondary outcomes will be compared between the treatment arms and expressed as relative risk with 95% CI. Results will be reported per-patient and per-(first) cycle. Time to pregnancy leading to a live birth will be visually compared in a Kaplan-Meier plot and formally compared using log-rank analysis. We will perform a subgroup analysis in which we will assess the effect of potential effect modifiers, like age, type of subfertility (primary or secondary) and duration of subfertility on the effectiveness of progesterone treatment. Attempts will be made to complete missing data (eg, by inquiring at the local sites). If data are still considered missing, cases will be listwise excluded. SPSS (IBM SPSS STatistics V29), RStudio and Excel will be used to perform the statistical analysis.^23^ A p value of <0.05 will be considered statistically significant.

Additionally, a cost-effectiveness analysis and a cost-utility analysis will be performed from a societal and healthcare perspective according to Dutch guidelines with a time horizon of 12 months.

Included cost categories are (1) healthcare costs (MOH-IUI treatment, progesterone capsules, costs of additional hospital visits and IVF treatment in case couples do not become pregnant) and (2) societal costs (mainly related to productivity costs due to treatment and hospital visits).

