Currently, there is no consensus on the use of progesterone supplementation after MOH-IUI. A meta-analysis by Green *et al* in 2017 concluded that LPS could be effective in MOH-IUI, specifically in mild stimulation cycles using low-dose FSH, with live birth occurring more frequently in patients receiving exogenous progesterone (random-effects modelling, RR 1.76, 95% CI 1.29 to 2.40, p<0.001, number needed to treat 11).^16^ An updated and extended literature search and meta-analysis by Casarramona *et al*, in which four additional studies were included compared with the previous review in 2017, found comparable results to the Green review (single cycle; live birth rate RR 2.47, 95% CI 1.37 to 4.44; three randomised controlled trials (RCTs), 678 participants; cumulative live birth rate for up to six cycles: RR 1.49, 95% CI 1.17 to 1.90; five RCTs, 1027 participants).^17^ For both reviews, the level of evidence had been graded low to moderate. The studies in the meta-analysis are often single-centre based, fail to obtain individual power, were mostly not (double-) blinded, included only a single treatment cycle and/or evaluated various types of luteal support. Due to the overall moderate study quality and small to moderate size of the individual studies, the certainty of the evidence should be considered with caution and broad implementation of progesterone luteal support in MOH-IUI treatment cannot be justified with the current research data. The substandard evidence quality warrants a large, well-designed, well-powered trial to provide the evidence that is needed to confirm or dismiss the effect of progesterone LPS after MOH-IUI. For this purpose, the LUMO (LUteal phase support in Mild Ovarian hyperstimulation (MOH) for intra-unterine insemination (IUI)) study was designed, funded and is currently ongoing.

The primary aim of the LUMO study is to determine whether the addition of exogenous progesterone in the luteal phase of MOH-IUI treatment will lead to increased live birth rates and will provide the basis for application of this strategy in daily practice. The hypothesis is that the chance of pregnancy leading to live birth within a 6-month study period will increase from 30% to 39% after MOH-IUI treatment with LPS. In addition, the study seeks to evaluate the total budget impact of the addition of LPS in MOH-IUI treatment in terms of reduction in total budget spent on (in)fertility care through a cost-effectiveness analysis.

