### Eligibility criteria

Eligibility criteria are in line with the indication for MOH-IUI treatment and in accordance with current (Dutch) NVOG (Nederlandse Vereniging voor Obstetrie en Gynaecologie (Dutch Sciety for Obestrics and Gynaecology)guidelines.^18^ In the Netherlands, in couples with unexplained subfertility, the prognosis for spontaneous pregnancy in the year following the subfertility workup is calculated using the validated Hunault prognostic model.^19^ This model uses the predictive factors female age, subfertility duration, type of subfertility (primary vs secondary), sperm motility and referral status. When the likelihood of spontaneous pregnancy is <30% (or ≥30% after an expectant management period of at least six additional months), MOH-IUI is suggested as the primary treatment. To participate in the study, a participant must meet all of the following criteria: (1) diagnosis of unexplained subfertility; (2) Hunault <30% (or ≥30%, after an expectant management period of at least six additional months); (3) female age 18–43 years; (4) female body mass index (BMI) <45 kg/m^2^; (5) primary or secondary subfertility, for at least a period of 1 year (or, in case of secondary infertility with previous successful MOH-IUI treatment, an expectant management of at least 6 months); (6) regular menstrual cycle; (7) total motile sperm count >10 million (prewash/unprocessed) and (8) first MOH-IUI cycle (with gonadotropins), with the intent to receive this treatment for at least 6 months. Exclusion criteria are (1) uncorrected uterine factors, such as endometrial polyps or submucosal fibroids; (2) insufficient knowledge or understanding of the Dutch or English language and not willing or able to receive study information via a certified translator; (3) not able or willing to provide (written) informed consent and (4) contraindications for vaginal progesterone, particularly females with allergy to peanuts or soya.

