**Figure 1 F1:**
[figure not shown]
Overview of the main procedures that participants will undergo during standard MOH-IUI treatment and additional actions required for the LUMO trial. BMI, body mass index; FSH, follicle-stimulating hormone; HCG, human chorionic gonadotropin; IUI, intrauterine insemination; LH, luteinising hormone; MOH, mild ovarian hyperstimulation; VCM, total motile sperm count.

The study period is 6 months. Study medication is used after all MOH-IUI treatment cycles within this period. The follow-up period includes the subsequent 12 months after the end of the study period. During the study period and follow-up period, participants do not need to visit the hospital more frequently. There are no additional examinations or blood tests in addition to standard care. No invasive procedures need to be performed. Study participation ends 18 months after randomisation.

A total of three questionnaires will be sent during the study period. At randomisation, questionnaire 1 (Q1) will be sent that contains questions regarding quality of life (FertiQoL). 6 months after randomisation, questionnaire 2 (Q2) will be sent. This questionnaire contains questions regarding quality of life (FertiQoL), compliance to therapy and side effects. Questionnaire 3 (Q3) will be sent 18 months after randomisation. In the case of an ongoing pregnancy within the study period, questionnaire Q3A is sent that contains questions about the pregnancy (complications), delivery and perinatal outcomes. Questionnaire Q3B is sent in case a couple did not achieve an ongoing pregnancy during the study period. This questionnaire contains questions regarding information on the use of additional ART. After every MOH-IUI cycle during the study period, the online medication diary keeps track of compliance to therapy and side effects.

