### Outcomes

The primary outcome is cumulative pregnancy achieved within 6 months after randomisation, leading to live birth rate. Secondary outcomes include (1) progression to in vitro fertilisation (IVF); (2) multiple pregnancy rate; (3) time to pregnancy leading to live birth; (4) pregnancy complications (ie, hypertensive pregnancy disorders, blood loss during early pregnancy, preterm delivery); (5) perinatal outcomes (ie, stillbirth, birth weight, gestational age at delivery, congenital anomalies); (6) delivery outcomes (ie, type of delivery: spontaneous/induced, vaginal/caesarean, blood loss >1 L during delivery, manual removal of placenta); (7) side effects (incidence of common side effects: headache, vaginal discharge/itching, stomach ache, fatigue, nausea and uncommon/other side effects); (8) compliance to therapy; (9) quality of life; (10) number of adverse events (AEs) and serious adverse events (SAEs); and (11) cost-effectivity.

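### Relative risk is prescribed for all primary and secondary outcomes, but birth weight, gestational age and FertiQoL score are not binary and the article gives no cut-points for them

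*Protocol article*

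**What the plan says.** The effect measure is fixed in one unqualified sentence of the protocol article (Data collection and data analysis): "Primary and secondary outcomes will be compared between the treatment arms and expressed as relative risk with 95% CI". The same section departs from it twice. Time to pregnancy gets a Kaplan-Meier plot and a log-rank test, and costs get a separate economic analysis.

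The Outcomes section gives the primary endpoint as follows: "The primary outcome is cumulative pregnancy achieved within 6 months after randomisation, leading to live birth rate". That is a yes/no result per couple. Among the secondary outcomes it lists "perinatal outcomes (ie, stillbirth, birth weight, gestational age at delivery, congenital anomalies", and also quality of life and the number of adverse and serious adverse events.

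On quality of life, the Study timeline section says: "At randomisation, questionnaire 1 (Q1) will be sent that contains questions regarding quality of life (FertiQoL"). The questionnaire sent at 6 months asks about FertiQoL again, so each woman can have a baseline and a follow-up score.

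On baseline factors, the Eligibility criteria section describes the Hunault model for spontaneous pregnancy: "This model uses the predictive factors female age, subfertility duration, type of subfertility (primary vs secondary), sperm motility and referral status". In the analysis section, age and type and duration of subfertility appear only as potential effect modifiers for subgroup analysis. The article does not say whether the primary relative risk is adjusted.

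**The concern.** A relative risk compares two proportions, so it needs a binary outcome. Birth weight and gestational age are continuous and FertiQoL is a score. To follow the sentence literally, someone would have to choose a threshold for each, and the article states none. A threshold chosen once data are in hand leaves room for selective reporting, and splitting a continuous measure discards information. For FertiQoL, a comparison of proportions at 6 months would also make no use of the score collected at randomisation.

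This is more than an omission that a statistical analysis plan would fill. The article makes a positive statement, and a sensible analysis plan would have to depart from it.

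At stake are the interpretability and precision of a few secondary outcomes. The primary comparison is not in question.

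**Working it through.** **1. Which outcomes fit the stated measure**

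- Binary as listed, so a relative risk is computable: the primary outcome, progression to IVF, multiple pregnancy, stillbirth, congenital anomalies, preterm delivery, type of delivery, blood loss above 1 L, manual removal of the placenta, and incidence of each side effect.
- Given their own method: time to pregnancy and cost-effectiveness.
- Neither binary nor given another method: birth weight, gestational age at delivery, FertiQoL score, and number of adverse and serious adverse events.

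Preterm delivery appears as a separate binary outcome, so it does not tell us how gestational age itself would be analysed.

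**2. What a baseline-adjusted analysis of FertiQoL would gain**

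The article gives no correlation between the two FertiQoL scores, so I assume ρ = 0.5 to 0.7. Relative to comparing 6-month scores alone, ANCOVA multiplies the variance of the arm difference by 1 − ρ²:

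- ρ = 0.5: 1 − 0.25 = 0.75, a cut of 25%.
- ρ = 0.7: 1 − 0.49 = 0.51, a cut of 49%.

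For illustration only, splitting a normally distributed score at its median keeps about 2/π = 0.637 of the information. A median split that ignored baseline would then use 0.637 × 0.75 = 0.478 to 0.637 × 0.51 = 0.325 of what ANCOVA would use. The article does not say that a median split is planned.

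**3. The sample size as a reference point for the primary outcome**

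Inputs: a rise in the live birth outcome, "increase from 30% to 39% after MOH-IUI treatment with LPS" (Introduction); "479 couples in each treatment arm would provide 80% power, with confidence level 95% to detect the predicted difference of 9" percentage points (Sample size); "A p value of <0.05 will be considered statistically significant" (Data collection and data analysis). I take the test as two-sided, which is not stated.

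With p̄ = (0.30 + 0.39)/2 = 0.345, the pooled formula is

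n = [1.96 × √(2 × 0.345 × 0.655) + 0.8416 × √(0.30 × 0.70 + 0.39 × 0.61)]² / 0.09²
= (1.318 + 0.563)² / 0.0081, which rounds up to 437 per arm.

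With a continuity correction it is 459. Neither equals the stated 479, so that figure is not reproduced, but the difference is on the safe side. At 479 per arm:

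z = (0.09 × √479 − 1.318) / 0.669 = 0.974, so power is 83.5%.

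Power by Fisher's exact test is 81.9%. Both exceed the planned 80%. This difference has no bearing on the effect-measure point.

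**4. What covariate adjustment of the primary outcome might add**

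The article gives no strength for any predictor of live birth after MOH-IUI, so I assume a prognostic score with AUC of about 0.60 to 0.65. With a normal linear predictor of SD 0.36 or 0.545 at an overall rate of 34.5%, the share of outcome variance explained is R² = 0.028 or 0.060. Treating adjustment as raising the effective size to 479/(1 − R²):

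- R² = 0.028: 479/0.972 = 493, power 84.5%.
- R² = 0.060: 479/0.940 = 510, power 85.7%.

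The gain is about one to two percentage points.

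**The case against.** The best defence is that the sentence is shorthand. The same section gives time to pregnancy and costs their own methods, most of the listed secondary outcomes are proportions for which relative risk is suitable, and no statistician would compute a relative risk for birth weight. It can be added that the article nowhere says a score will be dichotomised or that the baseline FertiQoL will be ignored. That last point is correct: both would follow from reading the sentence literally, and neither is a stated intention. The defence makes the fault minor but does not remove it. Exceptions were named where they were wanted, and continuous outcomes are not among them.

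A reader might go further and infer that the primary relative risk is unadjusted and so wastes strong baseline predictors. The documents do not support this:

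- The word unadjusted does not appear, and an adjusted relative risk fits the same sentence. The choice of covariates is commonly left to an analysis plan.
- The named factors belong to a model for spontaneous pregnancy, not for live birth after MOH-IUI, and no strength is given. Couples are also selected partly on that score, which may narrow its spread.
- An unadjusted relative risk is valid in a 1:1 randomised trial. Its confidence interval already allows for chance imbalance, and the article names no stratification factor that the analysis would have to honour.

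Two cautions about the remedy also stand. The analysis section excludes cases with missing data listwise, so adding covariates carelessly could lose couples. And birth weight and gestational age exist only for women who deliver, a group formed after randomisation that treatment may change.

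**Conclusion.** The point holds for the effect measure. As written, the article prescribes relative risk for birth weight, gestational age at delivery and FertiQoL score, where it cannot be computed without thresholds that are not given, and for a number of adverse events, which must first be expressed as a proportion or a rate. This should be corrected, but it touches secondary outcomes only. It does not affect the primary outcome or the sample size.

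The only sizeable statistical gain is for FertiQoL: a 25–49% smaller variance from using the baseline score, resting on an assumed correlation of 0.5–0.7.

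Covariate adjustment of the primary outcome is an optional efficiency gain. The figures of 84.5–85.7% against 83.5% rest on assumed AUCs of 0.60–0.65, and the trial exceeds its planned 80% power without adjustment.

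**What to change.** Reword the analysis section, or settle the matter in the analysis plan before unblinding:

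- Restrict relative risk with 95% CI to binary outcomes.
- Analyse FertiQoL at 6 months as a mean difference from ANCOVA, adjusted for the score at randomisation.
- Report mean differences for birth weight and gestational age, and describe them as comparisons among women who deliver, a subset formed after randomisation.
- Report adverse and serious adverse events as the proportion of women with at least one event, or as a rate.

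Optionally, prespecify for the primary outcome a relative risk and risk difference adjusted for female age and for duration and type of subfertility. Logistic regression with marginal standardisation, or modified Poisson regression with robust standard errors, would do this. Keep the unadjusted relative risk as support, and state that no couple is dropped for a missing covariate, which means exempting covariates from the listwise exclusion rule.

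The cost is wording and a little programming. The baseline FertiQoL score and these covariates are already collected, and recruitment is still under way according to the Study status section.

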#### Withdrawal

Participants can leave the study at any time for any reason if they wish to do so, without any consequences. The investigator can decide to withdraw a participant from the study for urgent medical reasons. In the case of withdrawal of consent, outcomes will be imputed using all information obtained before withdrawal of consent.

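### The plan excludes cases with missing data listwise, which conflicts with its intention-to-treat statement and is not reconciled with its rule to impute outcomes after withdrawal

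*Protocol article*

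**What the plan says.** Three statements in the protocol article bear on a couple whose live-birth status is unknown.

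- Data collection and data analysis, on the analysis principle: "All statistical analysis will be done according to the intention-to-treat principle".
- The same section, on missing data: the team first tries to complete the data, for instance by asking the local sites. For what remains, "If data are still considered missing, cases will be listwise excluded".
- Withdrawal: "In the case of withdrawal of consent, outcomes will be imputed using all information obtained before withdrawal of consent".

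The Sample size section sets the expected scale of loss: "To correct for potential dropout (±5%), the aim is to include a total of 1008 patients (504 patients in both groups". It does not divide that loss between the arms and says nothing about the outcomes of those lost. The effect measure for primary and secondary outcomes is the relative risk with a 95% confidence interval.

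**The concern.** There are two problems in the text itself.

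First, a couple who withdraws consent and has no recorded birth outcome falls under both the imputation rule and the exclusion rule. The first keeps the couple in the analysis and the second removes it. No order of precedence is given.

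Second, the intention-to-treat statement is unqualified, yet the exclusion rule in the same section removes randomised couples. This problem remains even if withdrawals are set aside, because it covers every other missing primary outcome.

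The primary outcome makes this more than a matter of wording. It is a pregnancy achieved within 6 months that leads to a live birth. According to the Study timeline section there are no extra hospital visits, and the questionnaire on pregnancy and delivery goes out 18 months after randomisation. A couple with a known ongoing pregnancy but no confirmed delivery could therefore be dropped, and the knowledge of that pregnancy would be lost with it. At stake is whether the primary relative risk compares the groups as randomised.

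**Working it through.** **Inputs.** From the Sample size section: 30% on placebo, 39% with luteal phase support (LPS), a 9-point difference, 479 couples per arm before dropout, 504 after, and about 5% dropout. The relative risk (RR) is 39/30 = 1.30.

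**The plan's own figures.** The dropout step reproduces: 479/0.95 = 504.2. The number lost is 504 × 0.05 = 25.2, so about 25 per arm or 50 in all. The 479 itself is larger than standard two-sided 5% formulas give for 80% power (437 per arm, or 459 with continuity correction; two-sided testing is assumed). That is conservative and does not affect this point.

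**Check 1: what listwise exclusion does to known full-cohort rates.** Suppose the full-cohort rates are exactly 39% and 30%. The expected births are 0.39 × 504 = 196.56 and 0.30 × 504 = 151.2. If m couples are lost in an arm and b of them had a birth, the complete-case rate is (births − b)/(504 − m). The last column is (difference − 9)/9. Every loss pattern below is an assumption.

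| Lost, LPS/placebo | Outcome of those lost | Difference (points) | RR | Shift |
|---|---|---|---|---|
| 25/25 | random | 9.00 | 1.30 | 0% |
| 25/25 | no birth | 9.47 | 1.30 | +5% |
| 25/25 | all births | 9.47 | 1.36 | +5% |
| 15/35 | no birth | 7.96 | 1.25 | −12% |
| 35/15 | no birth | 10.99 | 1.36 | +22% |
| 10/40 | no birth | 7.20 | 1.22 | −20% |
| 40/10 | no birth | 11.75 | 1.38 | +31% |
| 0/50 | no birth | 5.70 | 1.17 | −37% |
| 50/0 | no birth | 13.30 | 1.44 | +48% |
| 10/40 | all births | 13.80 | 1.58 | +53% |
| 40/10 | all births | 5.16 | 1.18 | −43% |
| 25/25 | LPS all births, placebo none | 4.25 | 1.13 | −53% |
| 25/25 | LPS none, placebo all births | 14.69 | 1.56 | +63% |
| 50/0 | all births | 2.28 | 1.08 | −75% |
| 0/50 | all births | 16.71 | 1.75 | +86% |

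Worked example, 15/35 with no birth: 196.56/489 − 151.2/469 = 0.4020 − 0.3224 = 0.0796.

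In whole births (197 and 151), the two opposite-outcome rows become 172/479 − 151/479 = 4.4 points (RR 1.14) and 197/479 − 126/479 = 14.8 points (RR 1.56).

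**Check 2: what a rule that keeps everyone would show.** Suppose instead that 39% and 30% are observed in 479 couples per arm, with 25 per arm missing.

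- Missing counted as no birth: 0.39 × 479/504 = 37.1% and 0.30 × 479/504 = 28.5%. The difference is 8.55 points and the RR 1.30.
- Least favourable to LPS (missing LPS none, missing placebo all births): 37.1% and (0.30 × 479 + 25)/504 = 33.5%. The difference is 3.6 points, RR 1.11, p about 0.23.
- Most favourable: (0.39 × 479 + 25)/504 = 42.0% and 28.5%. The difference is 13.5 points and the RR 1.47.

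**The case against.** The best defence is that the two rules belong to different cases. The Withdrawal section is specific, the exclusion rule is residual, and an outcome that has been imputed is arguably no longer missing. A reader might infer a flat contradiction in which the two rules can never coexist. The text does not support that, because the specific-then-residual reading is possible. But the article does not state that order, and the reading does nothing for the conflict with intention to treat over all other missing outcomes.

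The defence can also point to safeguards. Missing data are first sought from the sites, a questionnaire goes at 18 months to couples with and without an ongoing pregnancy, and the trial is double-blind, which makes strongly arm-dependent loss less likely. These points stand. They reduce the amount and imbalance of missing data without settling how the remainder is handled.

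A reader might also infer that the rule could be chosen after the results are seen. The article does not show this. Allocation stays concealed until database lock, and an analysis plan that is not shown may settle the order beforehand. Such a plan would still have to depart from one of the article's published statements.

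Finally, a particular imputation model is a matter of preference and is properly left to the analysis plan. That is accepted.

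**Conclusion.** The point holds as an inconsistency in stated rules. Followed as written, the exclusion rule removes randomised couples from the primary relative risk while the same section claims intention to treat, and its relation to the imputation rule for withdrawals is undefined.

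A reader might infer that the rule will shift the primary effect by about half its planned size. The documents do not support that as an expectation. In the patterns tried, a shift of about half or more arises only when the missing couples have opposite outcomes by arm, or when at least 40 of the 50 losses fall in one arm; in the 40-of-50 case this also required those lost to be births. For balanced loss the difference moves by 0% to 5%, and the RR stays at 1.30 when those lost had no birth. Moderately unequal loss of couples without a birth gives shifts of about 12% to 31%, in either direction.

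All of these sizes assume 5% missing and the planned rates. The split by arm and the outcomes of those lost are not in the article, so the figures are a range of possibilities and not an estimate of bias.

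**What to change.** Remove listwise exclusion for the primary outcome. State one rule, worded the same under Withdrawal and under Data collection and data analysis, that keeps every randomised couple in the assigned arm. It should handle missing live-birth status with the information already collected, including last known pregnancy status. Multiple imputation is one suitable method; the choice of predictors can be left to the analysis plan. Keep the step of querying the sites first.

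Add two sensitivity analyses for the primary outcome: missing counted as no live birth, and a best/worst-case or tipping-point analysis that varies the assumed outcomes by arm.

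The cost is a change of wording and a little extra analysis. No new data are needed. The article reports that recruitment is ongoing and allocation is concealed until database lock, so the rule can still be fixed blind.

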## Methods and analysis

### Design and setting

The LUMO study is a multicentre, double-blind, randomised-controlled trial with cost-effectiveness analysis. It is coordinated by the UMC Utrecht, Netherlands, and will be performed within the Dutch Consortium for Healthcare Evaluation and Research in Obstetrics and Gynecology. There are two treatment arms (A LPS; B placebo, non-crossover). All initiated MOH-IUI cycles within 6 months after randomisation are included (study period). Follow-up period ends 12 months after the end of the study period (18 months after randomisation). The primary outcome is cumulative pregnancy, achieved within 6 months after randomisation, leading to live birth rate. The aim is to include 1008 patients (504 patients in each group).

At present, there are 33 sites (fertility clinics, academic and non-academic hospitals) participating in the LUMO study. All participating sites and their corresponding local principal investigator are mentioned in the ‘Acknowledgements’ section.

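### The 12-month horizon of the economic evaluation does not match the 18-month follow-up: it cuts off half of the IVF window and the later qualifying births

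*Protocol article*

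**What the plan says.** All of this is in the Protocol article.

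- **Horizon.** Under Data collection and data analysis, both economic analyses are planned "from a societal and healthcare perspective according to Dutch guidelines with a time horizon of 12 months". No start point, effect measure or reason for the 12 months is given.
- **Costs.** The same section lists, as healthcare costs, insemination treatment, progesterone capsules, and "costs of additional hospital visits and IVF treatment in case couples do not become pregnant". Productivity costs are the main societal item.
- **Effect.** Under Outcomes: "The primary outcome is cumulative pregnancy achieved within 6 months after randomisation, leading to live birth rate".
- **Follow-up.** Under Design and setting: "Follow-up period ends 12 months after the end of the study period (18 months after randomisation").
- **Data collection.** In the timeline text after Figure 1: "Questionnaire 3 (Q3) will be sent 18 months after randomisation". One version covers pregnancy, delivery and perinatal outcomes. The other goes to couples without an ongoing pregnancy in the study period: "This questionnaire contains questions regarding information on the use of additional ART".
- **Purpose.** The Introduction names the effect on total spending on fertility care as an aim. The Discussion expects part of the gain to come from fewer couples needing IVF.

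**The concern.** A horizon should be long enough to hold the costs and effects that differ between the arms. Here the intervention is given in months 0 to 6, the resulting births run past month 12, and the IVF that might be avoided comes mostly after month 6. Eligibility asks for the intention to have at least 6 months of insemination treatment. The trial observes all of this to month 18, but the stated horizon stops at month 12.

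Two things are at stake. IVF savings arising after month 12 would be left out of the base case although couples are followed for them. And, depending on an effect measure the article does not name, either the effect is cut short or births are counted as effects while the costs of the same months are not.

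**Working it through.** **1. The plan's own figure.** The timeline text states: "The study period is 6 months". Follow-up adds 12 months, so 6 + 12 = 18 months after randomisation, as stated.

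**2. Which 12 months?**

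| Window | Insemination and progesterone costs (months 0–6) | Term births (to about month 14.7) | IVF in months 6–18 |
|---|---|---|---|
| Months 0–12 | inside | partly outside | half outside |
| Months 6–18 | outside | inside | inside |

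The second window would drop the treatment costs that the plan lists, so the first is the more natural reading. Neither holds intervention, outcome and follow-up together.

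**3. IVF window.** The share outside is (18 − 12)/(18 − 6) = 6/12 = 50%. This is calendar time, not a share of IVF cycles or costs. The article gives no IVF uptake or unit cost, so the lost saving cannot be put in euros.

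**4. Births after month 12, central case.** Inputs from the article: conception window 0 to 6 months; design rates 30% and 39% (Sample size). Assumptions not in the article: horizon from randomisation, 40 weeks' gestation, constant conception hazard.

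- Conception to birth: (40 × 7 − 14)/30.44 = 266/30.44 = 8.74 months.
- Latest qualifying birth: 6 + 8.74 = month 14.7.
- Latest conception born by month 12: 12 − 8.74 = month 3.26.
- Monthly hazard λ = −ln(1 − p)/6: 0.0594 for p = 0.30 and 0.0824 for p = 0.39.
- Born by month 12 = 1 − exp(−3.26λ): 17.6% (placebo) and 23.5% (progesterone).
- Share of qualifying births outside: 1 − 0.176/0.30 = 41% and 1 − 0.235/0.39 = 40%.

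**5. Other timing assumptions.**

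| Conception timing | Gestation (weeks) | Share born after month 12 |
|---|---|---|
| Uniform over 6 months | 38 / 39 / 40 | 38% / 42% / 46% |
| Constant hazard | 38 / 39 / 40 | 32–34% / 36–38% / 40–41% |
| Discrete cycles of 28, 30 or 35 days | 38–40 | 28–46% |
| First insemination delayed 0.5–1.5 months | 40 | 44–57% |
| Front-loaded (Weibull shape 0.6–0.8) | 38–40 | 21–34% |

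Widening gestation to 37–41 weeks stretches the extremes to 18% and 62%.

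**6. Effect on the difference, if only births by month 12 count.** 23.5 − 17.6 = 5.9 points, against 39 − 30 = 9. Since 9/5.9 ≈ 1.5, the cost per additional live birth would rise about 1.5-fold through the denominator alone. If the effect is the primary outcome, dated by conception, the difference stays at 9 points and this factor is 1.

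**7. With an 18-month horizon.** The latest term birth (about month 14.7) and all of months 6 to 18 lie inside, so nothing in steps 3 and 4 is lost.

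**The case against.** The strongest reply is that the article names no effect measure, and that the only effect it defines, the primary outcome, is dated by conception. Every qualifying event is then achieved by month 6, inside the horizon, and no effect is lost. That stands. A reader might infer that the plan commits itself to a truncated effect and an inflated cost per live birth; the text does not support this, and the 1.5-fold figure is conditional. The reply does not rescue the cost side: IVF after month 12 is outside on either choice of effect, if the horizon starts at randomisation.

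Two further inferences are tempting.

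- *Delivery and neonatal costs are wrongly omitted.* The Introduction frames the budget question around fertility care, so leaving obstetric and neonatal care out can be a deliberate scope choice. A short list in an article is also no full costing plan.
- *IVF after a pregnancy loss will not be costed.* This reads too much into a short parenthesis. The questionnaire on further assisted reproduction goes to couples without an ongoing pregnancy from the study period, which includes those with an early loss and no later ongoing pregnancy. Progression to IVF is also a secondary outcome without that restriction.

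It is also fair that cost-effectiveness is the last of eleven secondary outcomes, and that data to month 18 are planned, so no information is lost if the horizon is changed.

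**Conclusion.** The mismatch is real and should be fixed. Counted from randomisation, the 12-month horizon excludes exactly half of the calendar window from month 6 to month 18. This is where much of the IVF saving argued for in the Discussion would appear. About 40% of primary-outcome births also fall after it. That share is modelled rather than stated: it rests on a constant hazard and 40 weeks' gestation, and runs from roughly 20% to 57% under the other timings tried at 38 to 40 weeks. What follows for the effect depends on the unnamed measure: about 5.9 points instead of 9 if births are counted by date, or an intact effect with costs and effects over different periods if the primary outcome is used.

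The start at randomisation is an inference from the listed costs. Counting from month 6 instead would exclude the treatment costs. The primary analysis, the sample size and the safety data are unaffected.

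**What to change.** - Set the base-case horizon of both economic analyses to 18 months and state that it starts at randomisation.
- Name the primary outcome (conception within 6 months leading to live birth, whatever the birth date) as the effect measure of the cost-effectiveness analysis.
- Cost IVF and other assisted reproduction to month 18 in all couples without an ongoing pregnancy from the study period, and say explicitly that couples with a pregnancy loss are included.
- Keep 12 months as a scenario. Delivery and neonatal costs can be added as an optional scenario from the outcome data already planned.

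The cost is a wording change and slightly more costing work, without extra visits or questionnaires. It is best made before unblinding, so that the choice of horizon cannot look driven by the results.
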